## Abstract

**Background::**

A comprehensive geriatric assessment (CGA) of elderly patients is useful for detecting the patients vulnerabilities. Exercise and early rehabilitation, nutritional intervention, traditional Chinese medicine (TCM), standardized medication guidance, and patient education can, separately, improve and even reverse the physical frailty status. However, the effect of combining a CGA and multi-disciplinary management on frailty in elderly patients remains unclear. The present study assessed the effects of a CGA and multi-disciplinary management on elderly patients with frailty in China.

**Methods::**

In this study, 320 in patients with frailty ≥70 years old will be randomly divided into an intervention group and a control group. The intervention group will be given routine management, a CGA and multi-disciplinary management involving rehabilitation exercise, diet adjustment, multi-drug evaluation, acupoint massage in TCM and patient education for 12 months, and the control group will be followed up with routine management for basic diseases. The primary outcomes are the Fried phenotype and short physical performance battery (SPPB). The secondary outcomes are the clinical frailty scale (CFS), non-elective hospital readmission, basic activities of daily living (BADL), 5–level European quality of life 5 dimensions index (EQ-5D), nutrition risk screening-2002 (NRS-2002), medical insurance expenses, fall events, and all-cause mortality. In addition, a cost-effectiveness study will be carried out.

**Discussion::**

This paper outlines the protocol for a randomized, single-blind, parallel multi-center clinical study. This protocol, if beneficial, will demonstrate the interaction of various intervention strategies, will help improve elderly frailty patients, and will be useful for clinicians, nurses, policymakers, public health authorities, and the general population.

**Trial registration::**

Chinese Clinical Trials Register, ChiCTR1900022623. Registered on April 19, 2019, http://www.chictr.org.cn/showproj.aspx?proj=38141.

## Introduction

1

Aging is an important public health issue all over the world. Frailty is a nonspecific state characterized by decreasing muscle strength, endurance and physiological reserves that may occur as the result of a variety of diseases and clinical conditions, resulting in increased vulnerability and a decreased anti-stress ability in elderly individuals.^[1]^ The prevalence rate of frailty increases with age, being around 10% in people ≥65 years old and 25% to 50% in people >85 years old.^[2]^ In addition, the prevalence rate of frailty is higher in medical institutions than in community-residing elderly.^[3–5]^ It seriously affects the function and quality of life of the elderly and poses a great threat to health life expectancy. Compared with non-frail elderly, frail elderly were shown to be more likely to suffer negative clinical events and require substantial medical resources.^[6]^ Several large epidemiological studies showed that frailty was strongly related to a poor prognosis of individuals, and it was an independent predictor of falls,^[1]^ deterioration of the function,^[1]^ decreased mobility,^[7]^ hospitalization, and death.^[8]^

Intervention studies on frailty around the world are still in their infancy.^[9–11]^ A few randomized controlled studies have found that multidisciplinary intervention can effectively treat and improve frailty in elderly patients.^[12–14]^ Exercise and early rehabilitation protocols applied during hospitalization can prevent functional and cognitive decline in older patients and were shown to be associated with a reduced length of stay and lower costs.^[15]^ Combined aerobic and resistance training can improve interventions in physical function and help reduce frailty.^[16]^ Exercise is likely the best therapy for reversing the frailty status, including aerobic, resistance, flexibility, and balance training components. More than 30% of medical inpatients are at an increased risk of malnutrition, a condition that is strongly associated with increased mortality and morbidity, medical resource use and a reduced functional ability.^[17]^ While nutritional intervention can improve a persons physical condition, traditional Chinese medicine (TCM) therapies appear to be effective for treating fibromyalgia, insomnia and constipation,^[18–20]^ and acupoint massage is an effective intervention for maintaining the cognitive function among older adults.^[21]^ Insomnia and constipation are common diseases in the elderly, so effective and simple acupoint massage may improve the symptoms of insomnia and constipation in daily life. Frail individuals tend to be affected by polypharmacy and are at an increased risk of adverse drug events. Standardized medication guidance is essential for improving the prognosis of elderly individuals with frailty.

A comprehensive geriatric assessment (CGA) of elderly patients is useful for detecting patients vulnerabilities,^[22]^ identifying elderly patients at high risk for mortality and poor recovery after surgery,^[23]^ and predicting outcomes independent of performance status among elderly patients.^[24]^ Multi-disciplinary intervention according to the CGA findings has been shown to improve the activity, anxiety and depression status, fall events, readmission rate, and quality of life score to a certain extent.^[25–27]^ Therefore, combining a CGA and multi-disciplinary intervention may be an effective means of improving frailty in elderly patients.

Hospitalization may lead to a decline in the function of elderly patients, and many elderly patients are unable to fully recover their physical function after hospitalization, which increases the risk of frailty, disability, dependence, re-hospitalization and death.^[28,29]^ This point therefore merits a thorough look.

In the present study, frailty will be measured using the definition of frailty syndrome established by Fried et al,^[1]^ and patients in the intervention group will undergo the CGA during hospitalization and start multi-disciplinary intervention that will last 12 months. If this study proves that the multi-disciplinary management model can improve the symptoms and prognosis of frail elderly patients, it will help improve the medical status of elderly frailty patients, save social public medical resources and provide assistance for the development of medical policies.^[30,31]^

## Methods

2

### Study design and setting

2.1

This is a multicenter, randomized, parallel controlled study. The study has been designed to determine the effect of a CGA and multi-disciplinary management on patients ≥70 years old with frailty in China.

The primary outcomes are the Fried phenotype,^[1]^ which presenting at least 3 of the following: unintentional weight loss, self-reported exhaustion, weakness, slow walking speed and low physical activity; and the short physical performance battery (SPPB), scored from 1 to 12 based on three tests (balance tests, gait speed and 5-sit-to-stand test; low score 0–6, medium score 7–9, high score 10–12).^[32]^ The secondary outcomes are the clinical frailty scale (CFS), which uses pictographs and clinical descriptions to help clinicians stratify elder adults on a 9-point scale (1 being very fit and 9 being terminally ill);^[33]^ non-elective hospital readmission,^[13]^ which is considered any type of emergency readmission; disability, which is assessed by basic activities of daily living (BADL: total score 6);^[34]^ health-related quality of life, which is evaluated by the 5–level European Quality of Life 5 Dimensions index (EQ-5D: index values range from 0 to 1, with higher scores indicating a better quality of life);^[12]^ medical insurance expenses; fall events; nutrition risk screening-2002 (NRS-2002: the total score ranges from 0 to 7, and a total score ≥3 indicates malnourishment),^[35]^ and all-cause mortality.^[36]^ A standard multiplication model will be used to estimate the quality adjusted life years (QALYs), which are calculated based on the EQ-5D or BADL.^[37]^ The enrollment, intervention allocation, follow-up and data analysis will be conducted according to the Standard Protocol Items: Recommendations for Interventional Trials (SPIRIT) statement.^[38,39]^

### Eligibility criteria

2.2

Inclusion criteria for recruitment: hospitalized and ≥70 years old; have a Fried phenotype ≥3; are living in Beijing for at least 1 year and able to participate in the follow-up of the study; are able to volunteer to participate and sign informed consent.

Exclusion criteria for recruitment: currently participating in other similar clinical trials; have been treated with regular (≥3 days per week) traditional Chinese medicine (TCM) or acupuncture or have received regular (≥3 days per week) nutritional supplements or received treatment at a rehabilitation facility within the last 3 months; have exercised regularly at moderate intensity over the past 3 months (maximum heart rate of 50% × (220 – age) during exercise);^[40]^ are unable to complete the SPPB (main result of the study); are unable to participate in and stick to exercise alone; will be residing in a hospital or care home, including community specialist nursing facilities, rehabilitation centers and intermediate care facilities in the coming year; have dementia or severe cognitive impairment; have other severe concomitant conditions impair the ability of the patient; have end-stage disease with a life expectancy <12 months; have any other conditions or events that researchers or therapists consider to be excluded.

### Termination and withdrawal criteria

2.3

In the course of the study, if the researchers consider that continuing to participate in the study will lead to adverse outcomes, then the subjects participation will be terminated and they will be asked to withdraw from the study. The subjects are also free to request withdrawal at any time.

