1.Nutrition aspectAssessment: Age, grip strength, daily physical activity, NRS-2002 score, clinical diagnosis (especially sarcopenia), laboratory results, human body composition analysis (Inbody 720), dietary survey.Advice: A reasonable dietary plan will be formulated by the nutritionist.2.RehabilitationAssessment: SPPB, physical fitness tests,^[46]^ including a 30-second sit-to-stand test^[47–49]^ to assess lower body strength, a 30-second arm curl test^[50]^ to assess upper body strength, a 2-minutes step test^[51]^ to assess the cardiopulmonary function and aerobic endurance, a chair sit-and-reach test^[52,53]^ to assess lower body flexibility, a back scratch test^[54]^ to assess upper body flexibility, and a time-up-and-go test (TUG)^[53,54]^ to evaluate dynamic balance and agility.Advice: A set of rehabilitation exercises will be taught, including breath adjustment, posture adjustment, guidance for contracting abdominal muscles and pelvic floor muscles, head and neck stretching, back scratching, sitting forward stretching, sitting elastic belt assisted upper limb movement, heel lifting and stepping. Each participant will be given a sports manual with exercise instructions and safety information. During the period of hospitalization, all training sessions will be carefully supervised by a rehabilitation physician experienced in therapeutic training. Participants will perform 3 to 20 repetitions for each exercise and 3 to 5 times per week for 12 months, and accurately record the frequency, time and feelings concerning exercise each week, gradually increasing to the maximum tolerance and safety intensity. Participants will also be encouraged to exercise on their own and walk for a few minutes each day.3.Multi-drug evaluationAssessment: Medication appropriateness index (MAI),^[55]^ review of the type, measurement and quantity of drugs used by patients during hospitalization.Advice: Pharmacists will participate in the administration of drugs to the participants, potentially harmful drugs or doses will be revised and patients will receive instructions concerning medication when discharged.4.TCMAssessment: TCM physicians will comprehensively and systematically assess the participants based on the TCM theory of syndrome differentiation, including a TCM tongue diagnosis and pulse diagnosis.Advice: TCM physicians will deliver guidance on performing acupoint massage related to constipation and insomnia, including Zhigou, Zusanli, Dachangshu, Neiguan, Shenmen, and Sanyinchiao. Each participant will be instructed on 0 to 4 related acupoints, and each acupoint will be massaged for 5 minutes every day.5.Patient educationNurses will issue a patient education manual to each participant, covering the basic introduction of frailty, fall prevention education, first-aid knowledge and cardiovascular medicine guidance. All participants in both groups will undergo routine management.

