
### Follow-up

2.7

Data will be collected from all participants at 4 points throughout the study: before the intervention and 3, 6, and 12 months after the enrollment. Brief telephone reviews will be conducted approximately 2 to 3 times per month for all participants to promote adherence to the intervention. Participants in both groups will receive at least 12 months of telephone follow-up after the completion of the assessment or intervention in order to assess the durability and sustainability of any influence identified once the intervention stops.

Participants in the intervention group will be defined as treatment-compliant if they complete at least 50% of the planned rehabilitation exercises and/or 50% of their planned nutrition guidance program and 50% of the acupoint massage prescribed by TCM within 12 months. Participants will be required to make records in the debilitating record book. The individual dietary plan, rehabilitation exercise instruction with pictures and safety information, medication instruction, diagram of acupoint massage and patient education manual will also be represented in the record book in order to increase patients compliance. Researchers will assess the actual completion through the above requirements at the end of the intervention.

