Statistical analyses: We will conduct an intention-to-treat (ITT) analysis for the primary analysis, including primary and secondary outcomes, with a per-protocol (PP) analysis used for the sensitivity analysis. The ITT population is defined as all randomized participants in the study, and the PP population is defined as all randomized participants who were actually compliant with their treatment. The participants clinical features will be compared between the intervention and control groups. Continuous variables will be expressed as the mean ± standard deviation in a normal distribution and median and interquartile range in a non-normal distribution, and categorical variables will be expressed as numbers and percentages. Baseline characteristics will be compared by χ^2^ tests or Fishers exact tests for categorical variables and *t*-tests or Wilcoxons rank sum tests for continuous variables. A covariance analysis will be used to analyze the Fried phenotype, SPPB and modified means of the 2 groups, taking the central effect of the test into account, and the 95% confidence interval (CI) of the difference between the 2 groups will be calculated. Only when the above 2 main indicators satisfy the statistical hypothesis (superior effect), can the hypothesis be considered valid. For time-event data, the Kaplan–Meier method will be used to estimate death, non-elective hospital readmission and fall events. A log rank test will be performed for the 2 groups. A Cox proportional-hazard regression model will be used to calculate the effect of potential risk factors on the events. We will summarize the number of enrollments and completion of each center, list the drop-outs, compare the total drop-out rate and list the reasons for termination in detail and compare the characteristics between those with missing outcome data and those who have completed follow-up. The safety evaluation table will be included to describe the number of adverse events and the incidence of adverse events, serious adverse events, adverse reactions and serious adverse reactions in the two groups. Statistical significance will be set at a 2-sided *P* value <.05.

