#### Adverse events: fractures associated with rehabilitation exercise

2.9.1

Severe adverse events: persistent or severe disability or dysfunction caused by rehabilitation exercise.

If adverse or severe adverse events occur, the relationship between them and the intervention will be assessed, the intensity and mode of intervention will be adjusted, the intervention will be suspended if necessary, and the participants will receive appropriate treatment. We will immediately provide a diagnosis and treatment and report the occurrence in a timely manner while compensating the participant according to the relevant laws and regulations of our country.

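### Section 2.3 makes a researcher-initiated stop a withdrawal from the study, which can cost outcomes the ITT analysis needs, and the per-protocol analysis cannot test that loss

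*Protocol article*

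**What the plan says.** All references are to the protocol article.

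- **Section 2.3, Termination and withdrawal criteria.** The trigger is "if the researchers consider that continuing to participate in the study will lead to adverse outcomes". The consequence is "the subjects participation will be terminated and they will be asked to withdraw from the study". Participants may also withdraw at their own request. Neither route separates leaving the intervention from leaving follow-up.
- **Section 2.9.1, Adverse events.** Adverse events are fractures linked to the rehabilitation exercise, and severe ones are lasting or serious disability or dysfunction that it causes. The intensity and mode of the intervention are adjusted, and "the intervention will be suspended if necessary". Leaving the study is not mentioned.
- **Section 2.7, Follow-up.** Data are planned from all participants at baseline and at 3, 6 and 12 months, with telephone contact in both groups. Compliance is defined for the intervention group only: half of the exercises "and/or 50% of their planned nutrition guidance program and 50% of the acupoint massage prescribed by TCM within 12 months".
- **Section 2.6, Intervention.** "Each participant will be instructed on 0 to 4 related acupoints".
- **Section 2.8, Statistical management and analyses.** "We will conduct an intention-to-treat (ITT) analysis for the primary analysis, including primary and secondary outcomes". "The ITT population is defined as all randomized participants in the study". For the co-primary outcomes, "A covariance analysis will be used to analyze the Fried phenotype, SPPB and modified means of the 2 groups". Per protocol (PP) is the one sensitivity analysis named, and it is restricted to compliant participants. Drop-outs are listed with reasons, and participants with and without outcome data are compared.

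**The concern.** An ITT analysis of everyone randomised needs outcomes from people who stop the intervention. Section 2.3 tells staff to take some of these people out of the study altogether. An analysis plan written later can model or impute such outcomes, but it cannot recover what was never measured.

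The loss is unlikely to be neutral. The trigger is an expected bad outcome, so it is prognostic. The adverse events defined in Section 2.9.1 arise from exercise that only the intervention arm receives, and Section 2.5.3 says that staff delivering the intervention know the allocation. A participant injured by the exercise would probably score worse on balance, gait speed and chair stands. Removing that participant would remove an effect of the intervention from a co-primary outcome. The same withdrawals would censor death, readmission and falls informatively, whereas the Kaplan–Meier, log-rank and Cox methods in Section 2.8 assume uninformative censoring.

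The PP analysis cannot show whether this has happened, because it selects further, and in one arm only.

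**Working it through.** **1. The sections side by side.** After a harm-related stop, Section 2.3 ends study participation, while Section 2.9.1 changes or pauses the intervention and leaves study status open. Sections 2.7 and 2.8 need outcomes from everyone. A site following Section 2.3 literally would hold no later visits for that participant. A site following Section 2.9.1 would hold them.

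**2. The plan's own sample-size figure (Section 2.4).** The largest evaluable sample is 256 (128 per group), with 15% attrition and at least 320 recruited.
- 256 / 0.85 = 301.2, which is 302 in two equal groups, not 320. By contrast 256 / 0.80 = 320. This mismatch is a surplus and a separate matter.
- 320 × 0.85 = 272 with an outcome (136 per group) and 48 without. Since 272 exceeds 256, the issue here is bias and not sample size.

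**3. Back-solved SDs.** The article gives none. For 80% power and two-sided 0.05, SD = difference × √(n/2) / (1.960 + 0.842).
- Fried: 0.39 × √64 / 2.802 = 1.11 criteria, where 0.39 = 0.80 − 0.41.
- SPPB: 1.44 × √50.5 / 2.802 = 3.65 points.
- With these SDs, power at 136 per group is 0.82 (Fried) and 0.90 (SPPB).

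**4. Possible bias if lost outcomes are simply absent.** Let m be the share lost in an arm and g how much worse the lost are than those observed. The observed mean exceeds the full mean by m × g, so bias = m(intervention) × g(intervention) − m(control) × g(control). All values of m and g below are assumptions.

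| Loss, intervention / control | Gap | Fried bias (% of 0.39) | SPPB bias (% of 1.44) | Two-sided rejection under the null |
|---|---|---|---|---|
| 15% / 15% | equal in both arms | 0 | 0 | 0.05 |
| 20% / 10% | 0.5 SD, both arms | 0.10 × 0.5 × 1.114 = 0.056 (14%) | 0.183 (13%) | 0.07 |
| 20% / 10% | 1 SD, both arms | 0.111 (29%) | 0.365 (25%) | 0.13 |
| 15% / 15% | 0.5 SD, intervention only | 0.15 × 0.5 × 1.114 = 0.084 (21%) | 0.274 (19%) | 0.10 |
| 15% / 15% | 1 SD, intervention only | 0.167 (43%) | 0.548 (38%) | 0.24 |

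The rejection rates use a normal approximation without baseline adjustment and apply to each endpoint alone. Both endpoints must succeed, so the joint rate is no higher than the single one. In every unequal row the bias favours the intervention.

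**5. What PP does.** If the programme is spread evenly over 12 months, an intervention participant stopped before month 6 cannot reach half of any component that was prescribed, and so leaves the PP set. No rule filters controls. PP therefore drops the intervention participants in question and compares selected compliers with unselected controls.

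**6. Readings of the compliance rule.** R, N and T are adherence to exercise, nutrition and acupoint massage. Assume that each is met independently with probability p.

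| Reading | Formula | p = 0.4 | p = 0.6 | p = 0.8 |
|---|---|---|---|---|
| R and N and T | p³ | 6% | 22% | 51% |
| (R or N) and T | (1 − (1 − p)²) × p | 26% | 50% | 77% |
| R or (N and T) | 1 − (1 − p)(1 − p²) | 50% | 74% | 93% |

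The same data could make the PP intervention group small or nearly complete, depending on where the brackets go.

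**The case against.** Sections 2.3 and 2.9.1 can be read as a graduated response: adjust, then suspend, and withdraw only as a last resort. Section 2.3 also applies to either arm, and its trigger is expected harm from continuing, not poor progress as such. A reader might infer that losses fall mostly in the intervention arm. The documents do not show that. They show only that the adverse events they define can arise there and not from the control regimen.

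Section 2.8 also provides useful checks: drop-outs listed with reasons, total drop-out rates compared, and participants with missing outcomes compared with completers. These would help to reveal unequal loss, though they would not correct it. Participants stopped after month 3 or 6 will already have some outcomes, so the amount lost depends on the time point analysed.

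The article makes ITT primary and does not claim that PP repairs missing data. For participants with no acupoints prescribed, the sensible reading is that the massage component is met, so this is a gap in wording and not a rule that cannot be applied. Deaths are a separate matter from the withdrawal rule. The article analyses them as time to event, and their handling in the co-primary analyses may sit in a document not shown.

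What remains is that even the graduated reading ends in withdrawal from the study, and no section says that outcomes are still collected after it.

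**Conclusion.** The concern holds as a conflict between the withdrawal rule and the data that the analysis needs. Section 2.3, as written, ends outcome collection on a prognostic trigger, and the only sensitivity analysis named cannot test the consequence.

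The size is not known. It is zero if the share lost and the prognosis gap are equal across arms. In the assumed unequal scenarios it is about 14% to 43% of the planned 0.39 Fried difference and 13% to 38% of the planned 1.44 SPPB difference. These figures rest on assumed loss rates, assumed gaps of 0.5 to 1 SD and back-solved SDs. They illustrate what could happen and do not predict it. The informative censoring of death, readmission and falls was not quantified.

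A reader might go further and infer that the covariance analysis is complete-case, or that the declared ITT analysis is not ITT. The article supports neither. It writes no complete-case rule, it defines the ITT set correctly, and the handling of missing values is commonly left to an analysis plan, which is not shown here. The fault is that Section 2.3 does not secure the outcomes that a correctly defined set requires.

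**What to change.** 1. **Reconcile Sections 2.3 and 2.9.1.** Leave the decision on when to stop the intervention as it is. State that a participant whose intervention is stopped remains in the study for Visits 2 to 4 and telephone follow-up unless consent to follow-up is withdrawn. Record withdrawal from the intervention and withdrawal from follow-up separately, with reasons.
2. **Do not rely on PP as the only sensitivity analysis.** Add one for missing outcomes that applies the same rules to both arms. The choice of method can be left to the analysis plan.
3. **Rewrite the compliance rule in Section 2.7** with one explicit bracketing of the three components, and count participants prescribed 0 acupoints as meeting the massage component.

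The cost is a protocol clarification and some analysis-plan text. The visits and calls are already scheduled, so the practical burden is the effort of following people who have stopped the intervention. The change should be made promptly, since outcomes not collected cannot be recovered at analysis.
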